### **Exploratory Aim 1: Test whether participant churn can be predicted from objective measures of participant engagement with the gamified smartphone app**

An exploratory aim of the study is to identify objective measures of participant behavior on the gamified mobile app that predict retention, compliance, and engagement. Based on the behaviors of participants in the gamified mobile app group, we will use logistic regression and a random forest classifier to perform a survival analysis to predict participant “churn” (i.e. whether or not participants are retained at a given stage of the study). Churn will be predicted for the 3-month and 6-month milestones, based on participant behavior in the previous milestone (respectively at the 1-month and 3-month milestone). Features will include potential markers of engagement including the number of clicks on the avatar, number of changes made to the avatar, number of gem store purchases, and the total amount of time spent on the app. The importance of each feature will be explored to inform which features of the app most engage participants. The logistic regression and random forest classifier models will be compared based on their accuracy, precision, and the F1-score. A confusion matrix will be used to visualize the performance of the supervised learning algorithms; each row of the matrix represents the instances of the predicted class while each column represents the instances of the actual class. A range of thresholds (i.e. the probability threshold used to determine churn) will be explored to tune the accuracy and precision of the models.

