**Aim 5: Test whether gamification of cognitive tasks influences participant experience and technology acceptance.**

Hypothesis: Compared to participants who complete standard, non-gamified cognitive tasks (e.g., NIH Toolbox), participants who complete equivalent, gamified cognitive tasks within Datacubed Health's app will report a more positive experience on a usability/Technology Acceptance Model (TAM) questionnaire. Delivering cognitive tasks in a gamified format on mobile device will increase standard TAM outcomes (e.g., perceived ease of use, perceived usefulness, attitude towards using, behavioral intention to use).

**Exploratory Aim 1: Test whether participant churn can be predicted from objective measures of participant engagement with the gamified smartphone app**

Hypothesis: Participant churn (i.e. dropout) will be predicted by measures of participant engagement with the gamified smartphone app. This analysis will be restricted to Arm A participants assigned to the gamified smartphone app condition. Churn will be defined as missing more than 25% of assigned instruments within a study phase (the 1 month, 3 month, and 6 month milestones). Potential markers of engagement will included the number of clicks on the avatar, number of changes made to the avatar, number of gem store purchases, and the total amount of time spent on the app.

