### 3) BACKGROUND

The widespread availability and adoption of smartphones by people across all demographics and throughout the world has opened new and exciting frontiers of research that would have been unthinkable even ten years ago. The recent ubiquity of powerful computers with sophisticated graphics capabilities and built-in sensors that people carry with them all the time is beginning to transform research on health, behavior, and cognition. More and more research and clinical trials are going 'siteless,' opting to administer assessments remotely on mobile devices rather than in-person.

Missing data due to poor participant retention (i.e. dropout from the study and/or loss to follow-up) and compliance (i.e. missing or incomplete measurements) can jeopardize the scientific validity of studies and drive up the cost of conducting research and clinical trials. The National Academy of Sciences found patient dropout rates to be as high as 30% in clinical trials, prompting calls for better trial design and conduct to limit the impact of missing data. Missing data can threaten the scientific validity of findings by introducing unintended bias and reducing statistical power, increasing the possibility that studies will fail to find effects where they exist (i.e. Type II errors). Siteless clinical trials may face additional challenges, since remote studies leave participants to their own devices and may eliminate direct contact with members of the research team. Fortunately, technology and behavioral science offer an opportunity to address these challenges in novel ways by enabling more patient-centric practices to be implemented, which may ultimately accelerate research and drug development.

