## 9) STUDY DESIGN AND PROCEDURES

### Arms A-D

This study will employ at initial recruitment a between-subjects design with four, independent arms, divided into two sequential cohorts.

Each participant will first complete the informed consent process (see Section 29). Upon receipt of the signed consent (signature captured digitally), Datacubed Health will assign the participant

to one of 4 groups; group assignment will determine the medium through which the surveys will be administered -- gamified mobile app (Arm A), web browser (Arm B & Arm D), or paper (Arm C). Approximately 100 participants are expected to be enrolled into each group.

Group assignment will be done sequentially by date and time of consent signature – i.e., the first participant who signs consent will be assigned to Arm A; the second participant, to Arm B; the third participant, to Arm C; the fourth participant, to Arm D; the fifth participant, to Arm A; the sixth participant, to Arm B; etc. The first cohort of participants recruited into each arm will receive compensation every two weeks based on how many instruments they complete (\$5/instrument). The second cohort of participants recruited into each arm will receive a single payment at the conclusion of the 6-month arm. Compensation will be the same, \$5/instrument, but delivered as a single lump sum payment after completion. The maximum, total compensation possible in the initial 6-month study period will be \$130.

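### Exploratory Aim 1: accuracy, precision and F1, with the cut-off tuned on two of them, cannot by themselves show that engagement predicts churn

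*Protocol*

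**What the plan says.** Section 2 states the hypothesis for this aim: "Participant churn (i.e. dropout) will be predicted by measures of participant engagement with the gamified smartphone app". It limits the analysis to one arm ("This analysis will be restricted to Arm A participants assigned to the gamified smartphone app condition") and defines the outcome: "Churn will be defined as missing more than 25% of assigned instruments within a study phase".

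Section 11 (Data analysis plan, Exploratory Aim 1) predicts churn at the 3-month and 6-month milestones from behaviour up to the preceding milestone. The criteria it names are these: "The logistic regression and random forest classifier models will be compared based on their accuracy, precision, and the F1-score". A confusion matrix is to display performance, with predicted class in rows and actual class in columns. On the cut-off it says: "A range of thresholds (i.e. the probability threshold used to determine churn) will be explored to tune the accuracy and precision of the models". Feature importance is then to be used to learn which parts of the app engage participants most.

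For this aim the protocol names no reference value for a model without information and no threshold-free measure. It does not say on which data the cut-off is tuned or on which data performance is scored. The validation described next in Section 11 belongs to Exploratory Aim 2.

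**The concern.** The aim is framed as a test of whether engagement predicts churn, yet the only yardsticks are three measures whose values move with the churn rate. If few participants churn, a model that flags nobody has high accuracy. If many churn, a model that flags everybody has a respectable F1. Without the no-information value beside it, neither number says anything about engagement.

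The tuning sentence adds to this. Accuracy and precision are both the figures reported and the targets for choosing the cut-off. If the chosen cut-off is scored on the same predictions, part of the reported performance is the gain from the search.

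At stake is the claim that engagement markers predict churn, and the further inference about which app features matter. Importances from a model not shown to do better than chance cannot carry that inference.

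**Working it through.** **Inputs.** The sample is Arm A: "Approximately 100 participants are expected to be enrolled into each group" (Section 9). Four engagement markers are named, in a list that is left open: "Features will include potential markers of engagement including the number of clicks on the avatar, number of changes made to the avatar" (Section 11). The outcome is binary. The protocol states no churn rate, success criterion or target performance for this aim, so there is no planned figure to reproduce. The only dropout figure is background: "The National Academy of Sciences found patient dropout rates to be as high as 30% in clinical trials" (Section 3). It is not a planning rate for churn, so the churn rate p is an assumption below and a range is shown.

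**Step 1: values with no information.** Calling everyone the majority class gives accuracy max(p, 1 − p). Flagging people at random has expected precision p. Flagging everyone has precision p and recall 1, so F1 = 2p/(1 + p).

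| Assumed churn p | 10% | 20% | 30% | 40% | 50% |
|---|---|---|---|---|---|
| Accuracy, max(p, 1 − p) | 0.90 | 0.80 | 0.70 | 0.60 | 0.50 |
| Precision, p | 0.10 | 0.20 | 0.30 | 0.40 | 0.50 |
| Flag-everyone F1, 2p/(1 + p) | 0.18 | 0.33 | 0.46 | 0.57 | 0.67 |

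For example, at p = 0.30: F1 = 0.60/1.30 = 0.46.

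**Step 2: tuning the cut-off when there is no signal.** Simulated data had n = 100, four noise features independent of churn, and a logistic regression. The cut-off was chosen on the same predictions that were scored. Excess accuracy is measured against the majority-class rate. Excess precision is measured against the churn rate, taking the best precision with at least 5 people flagged.

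| Assumed churn | 20% | 30% | 40% |
|---|---|---|---|
| In-sample: runs with tuned accuracy above the majority rate | 56% | 83% | 96% |
| In-sample: mean excess accuracy | 0.01 | 0.02 | 0.05 |
| Cross-validated fits, cut-off tuned on the same predictions: mean excess accuracy | 0.002 | 0.005 | 0.014 |
| Same: runs with excess accuracy of 0.05 or more | 0.2% | 2% | 10% |

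Best precision exceeded the churn rate by about 0.27 to 0.31 in-sample, and by about 0.08 to 0.11 with cross-validated fits. At 30% churn, pure noise would thus show a precision of about 0.30 + 0.30 = 0.60 in-sample, or about 0.30 + 0.10 = 0.40 with cross-validated fits.

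**Step 3: the same kind of no-signal models on new data.** Here the cut-off (0.05 to 0.95) was set to maximise accuracy on the fitting data, and the models were scored on 1,000 fresh records.

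| Assumed churn | 10% | 20% | 30% |
|---|---|---|---|
| Logistic: accuracy / precision | 0.885 / 0.093 | 0.776 / 0.206 | 0.674 / 0.296 |
| Random forest: accuracy / precision | 0.813 / 0.102 | 0.660 / 0.204 | 0.553 / 0.296 |

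Precision returns to about the churn rate, and accuracy falls below the no-information value. Yet 0.81 to 0.89 at 10% churn would look good if printed without the churn rate.

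**Step 4: the model comparison, if scored on the fitting data.** A fully grown random forest gave 1.000 for accuracy, precision and F1 on pure noise at every churn rate tried. Logistic accuracy on the same basis was 0.809 at 20% churn and 0.714 at 30%. The forest would win by construction. This holds only under that kind of scoring, which the protocol does not specify.

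**The case against.** The best defence is that the protocol never says performance is scored on the data used for fitting. Data splitting, cross-validation and out-of-bag scoring are commonly left to a statistical analysis plan, which is not at hand. A reader might infer that the models will look predictive whenever engagement carries no signal, and that the forest is bound to win. The text does not support that reading. The forest's 1.000 figures need fully grown trees scored on their own data, and out-of-bag scoring would not show them. On new data the same measures, set against the churn rate, do not look predictive. Silence about held-out data is therefore not an error in itself.

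Four further objections carry weight.

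- F1 is reported but is not a tuning target; only accuracy and precision are.
- The measures are used to compare two models with each other. No pass/fail rule is stated.
- The share of runs that beat the majority rate sounds worse than it is. A search that can flag nobody or everybody cannot fall below that rate, and the average gain in accuracy is small.
- The column totals of the confusion matrix give the churn rate, so a careful reader could work out the no-information values. The precision figures also rest on one particular search rule, whereas the protocol only says that thresholds will be explored.

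What remains concerns what the protocol does state. It offers no other criterion for its hypothesis, it names measures that depend on prevalence, and it tunes the cut-off on two of them. Cross-validating the fits alone would not remove the inflation of precision. Being able to derive a benchmark is also weaker than a plan to report against it.

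**Conclusion.** The point holds in a limited form. As specified, accuracy, precision and F1 cannot by themselves show that engagement predicts churn, nor support conclusions from feature importance. The dependence on the churn rate follows from the definitions and needs no assumption about how scoring is done. The tuning effect depends on the cut-off being chosen on the scored predictions. It is then appreciable for precision (about 0.3 in-sample, about 0.1 with cross-validated fits) and slight for accuracy (at most about 0.05 and 0.014 on average at the churn rates tried). The forest's built-in advantage is conditional on scoring the fitting data and is not a stated feature of the plan.

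These sizes assume churn of 20 to 40%, about 100 participants, four independent noise features, and at least 5 people flagged where precision is maximised. Severity is low: the aim is exploratory and Aims 1 to 5 do not draw on it.

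**What to change.** Replace the tuning sentence in Section 11, Exploratory Aim 1, with text to this effect:

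> The probability threshold and any hyperparameters will be chosen only within inner (training) folds. Performance figures and feature importances will come from outer (held-out) folds. Cross-validated AUC with a confidence interval will be reported for each model at each milestone. Accuracy, precision, recall and F1 will be shown beside their no-information values: majority-class accuracy, churn prevalence and flag-everyone F1.

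Two models at two milestones give four AUCs. A permutation p-value, from shuffling the churn labels and repeating the whole procedure, may be added as descriptive support. It should not serve as a confirmatory gate, which would not suit an exploratory aim.

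The cost is a few sentences and some computing time, with no new data or participants. The downside is that reported performance will be lower and more variable than tuned in-sample figures. With about 100 participants and, say, 20% churn there are only about 100 × 0.20 = 20 events, so the intervals will be wide.

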### **Exploratory Aim 2: Develop novel markers of participant behavior and engagement based on objective information from app use**

Another exploratory aim of the study is to develop novel objective measures of participant behavior based on data from phone sensors (specifically phone location, step-counter, and screen on/off times). As noted in Section 3, such measures hold enormous potential to revolutionize the measurement of human behavior via data-driven assessment, as well as the prediction of health-related outcomes. Therefore, we plan to analyze phone sensor data collected in this study to further develop data-driven behavioral measures we have begun to develop using internal pilot data, and to validate those measures relative to self-reported information about individuals’ behavior (based on the activity tracker).

As an example, we plan to continue development of an algorithm to quantify individuals’ daily routines using a graph-theoretic approach based on mobility data (location & step-counter) and screen on/off data. First, these data will be preprocessed (normalized, resampled, and interpolated as necessary). Next, unsupervised clustering algorithms (e.g. DBSCAN) will be used to identify spatiotemporal patterns in the data (i.e., locations that the individual tends to frequent at regular times). Spatiotemporal areas of interest identified via the clustering analysis,

and periods of interstitial data between them (e.g. periods of travel from one location to another) will then be classified into different types of events using standard machine-learning techniques (e.g. random forest classification, neural networks). Then, we plan to transform the resulting information into an abstracted directed graph model of the individual's typical daily routine. Once a model of an individual's typical routine is established in this data-driven way, it can be used to quantify the amount and type of deviations from the routine captured in subsequent data using standard graph-theoretic metrics. In this study, we will further refine and develop these and other metrics for the data-driven characterization of behavior, then validate the accuracy of the resulting metrics using ground-truth data from the self-report activity tracker.

## **12) PROVISIONS TO MONITOR THE DATA TO ENSURE THE SAFETY OF SUBJECTS**

This study involves no additional risk to the subjects beyond what is encountered in daily life. There are no plans to monitor the safety of the subjects. If we receive information suggesting that a subject is at risk, they will be encouraged to call 911 or contact an emergency medical provider.

## **13) WITHDRAWAL OF SUBJECTS**

Subjects are free to withdraw at any time. They do so by contacting the study team by email. The study team will then delete their credentials from the Datacubed Health system after which the participant would no longer be able to access the app or websites beyond the initial login screen, and both the app and website would be unable to transmit any further data to the server. Subjects who were receiving their paper surveys by mail would not receive any subsequent surveys by mail, and the only further study-related contact required with the subjects would be to process any pending payments to date.

Subjects may also withdraw from the study by ceasing to return surveys. This will be identified as non-compliance rather than as a withdrawal.

When a subject withdraws from the study all data collected prior to withdrawal is retained. Subjects are informed of this at the time of consent.

## **14) RISKS TO SUBJECTS**

We do not anticipate any direct physical risks to the participant.

Risks to the subjects are minimal and do not exceed those encountered in daily life. Subjects may experience eye strain normally associated with reading and writing. Subjects will be informed that if they experience any discomfort of this kind they should cease the activity and rest before returning to the study-related task.

Participants may experience some psychological discomfort when answering survey questions that ask about thoughts, mood, or behaviors. Subjects are free not to answer any questions that they find uncomfortable.

The primary risk associated with this study is that an unauthorized party could gain access to study data and use it to identify participants. However, we have taken many precautions to ensure that this will not happen. The software systems we will use are built to protect the security of sensitive study data (see Sections 11 and 25). We will use safeguards such as strong encryption for all data on participants' phones, in transit to our servers, and on our servers. All access to study data will be password-protected and limited to authorized members of the study team. Other personnel involved in the development and maintenance of the software (e.g. the server administrator) will only have access to non-sensitive metadata (e.g. information about the date and time of failed data transmissions). Although we will do everything in our power to ensure the continued privacy and security of data from the study, unauthorized or unintentional disclosure of such data remains a minimal risk.

Geolocation data can also carry privacy risks for participants when the use, sharing, and handling of location data are not fully disclosed to participants. During the consent process, participants will be informed that the only use of geolocation data in this study is for comparison with self-reported survey data (i.e., to determine whether geolocation could serve as a novel measure of activity and routine); that the data will not be shared with any external parties; and that the data will be destroyed at the end of the study. Geolocation data will be handled in the same manner as PII.

#### **15) POTENTIAL BENEFITS TO SUBJECTS**

There is no benefit to the subjects from participation.

#### **16) VULNERABLE POPULATIONS**

We will not recruit minors or prisoners. We will not exclude pregnant women, so pregnant women could be included in our cohort. We will not solicit or record any information about whether one of our subjects is pregnant.

#### **17) MULTI-SITE RESEARCH**

This is a siteless study. Administration of the study and research team activities will occur at a single site: Datacubed Health.

#### **18) COMMUNITY-BASED PARTICIPATORY RESEARCH**

Not applicable.

#### **19) SHARING OF RESULTS WITH SUBJECTS**

No results will be shared with subjects.

#### **20) SETTING**

This is a siteless study; participants will be recruited via paper and internet advertisement (see section 6) and they will never visit a physical location to perform any study activities. The research team will be based at the offices of Datacubed Health.

## **21) RESOURCES AVAILABLE**

Datacubed Health will provide the resources necessary to conduct this study, including the necessary infrastructure and financial support. (Subjects will use their own smartphones, pencils/pens, and computers, as applicable.) The organization will provide access to and support for the app. Datacubed Health will provide compensation to those participants as they are assigned to receive it. Participants will earn \$5 for each week of successful survey completion; participants can thus earn anywhere between \$0 (if no surveys completed at all) to \$130 (if surveys are successfully completed over 6 months, or 26 weeks). Payments will be processed and distributed to participants every other week, for the first cohort of 50 participants enrolled in Arms A, B, C, and D (approximately 200 participants). Payments will be processed after 6 months for the second cohort of 50 participants enrolled in each arm (approximately 200 participants). Participants who choose to enter the optional two-week follow-up period will receive one PayPal transfer consisting of \$5 for each survey or task completed in that time, after two weeks.

The study team, who will be based at the offices of Datacubed Health, is composed of multiple well-qualified full-time researchers who will devote the time necessary to conduct and complete the study. Members of the team include:

- [name] (PI), a PhD level behavioral neuroscientist with a master of public health and over 10 years of research and evaluation experience, including in clinical and population health, as well as survey design, implementation, and analysis.
- [name] (Research Scientist), a PhD level behavioral neuroscientist with XX years of research and clinical trial experience
- [name] (Associate Research Scientist), a BS level scientist with graduate-level coursework in biostatistics and epidemiology and 2 years of experience developing and testing methods for mobile data collection
- [name] (Assistant Research Scientist), a BS level scientist with three years of experience coordinating clinical research trials, including in digital health.

All members of the research team have been involved in the design of the study and will have access to the IRB-approved protocol. The PI will take primary responsibility for the conduct of the study and will delegate specific duties to other members of the study team as necessary.

Since participants will be recruited from the New York City area, the inclusion criteria for the study are very broad, and the enrollment process is mostly automated, we believe it is entirely feasible to enroll the intended 400 participants within one year.

